## Abstract

**Introduction:**

Asthma and its associated exacerbation are heterogeneous. Although severe asthma attacks are systematically prescribed corticosteroids and often antibiotics, little is known about the variability of response to these therapies. Blood eosinophils and fractional exhaled nitric oxide (FeNO) are type 2 inflammation biomarkers that have established mechanistic, prognostic and theragnostic values in chronic asthma, but their utility in acute asthma is unclear. We speculate that the clinical and biological response to those treatments varies according to inflammometry and microbiological test results.

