**Trial registration number:**

ClinicalTrials.gov Registry (NCT05870215).

WHAT IS ALREADY KNOWN ON THIS TOPICAsthma exacerbations pose a substantial burden on healthcare systems and individuals. Despite existing knowledge, there are still gaps in our understanding of the precise mechanisms underlying asthma exacerbations, the role of biomarkers and the potential for more personalised treatment approaches.WHAT THIS STUDY ADDSPhenotyping the Responses to Systemic Corticosteroids in the Management of Asthma Attacks (PRISMA) is an observational longitudinal pilot study with multimodal clinical and translational assessments that aims to stratify the clinical and biological responses to systemic corticosteroids in asthma attacks according to type 2 inflammatory biomarkers (blood eosinophils and fractional exhaled nitric oxide) and will explore the relationship between other clinical, inflammatory biomarkers/proteins, and microbiological parameters and treatment response.HOW THIS STUDY MIGHT AFFECT RESEARCH, PRACTICE OR POLICYBy conducting an extensive array of clinical and translational assessments, this study aims to provide a holistic view of asthma attacks, shedding light on their multifaceted nature and paving the way for a comprehensive, larger-scale clinical trial.

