BEC and FeNO are effective biomarkers for several reasons. First, they provide complementary mechanistic information on different immune compartments involved in the pathogenesis of asthma. Blood eosinophilia is predominantly caused by circulating interleukin (IL)-5 activity and reflects the systemic component of type 2 inflammation,^15 16^ whereas FeNO elevation reflects the airway epithelial component mediated by IL-13-mediated inducible nitric oxide synthase.^16–18^ Second, they have additive and independent value in predicting severe asthma attacks in control arm trial populations across mild,^19^ moderate^20^ and severe asthma.^21–23^ Third, BEC and FeNO predict treatment response: raised levels are associated with greater benefit from anti-inflammatory therapies in chronic asthma, be it low-dose inhaled corticosteroids in mild disease,^19^ higher-dose inhaled corticosteroids in moderate^20 24^ or type 2 targeted biologics in moderate-to-severe asthma.^25–27^ Importantly, these biomarkers are simple, non-invasive and accessible.^14^ Just as high blood pressure and cholesterol levels are regularly assessed to predict and prevent heart attacks, BEC and FeNO are emerging as airway equivalents to quantify the modifiable risk of asthma attacks.^23 27 28^

The critical remaining questions are (a) how airway signalling (reflected by FeNO) and an increased systemic eosinophil pool (reflected by BEC) relate to the underlying biological pathways that contribute to asthma exacerbation and (b) how the type 2 inflammatory phenotype impacts the response to acute anti-inflammatory corticosteroid treatment. An often-cited confounder is airway infection, which is difficult to diagnose when relying on conventional sputum cultures but can indicate either greater susceptibility to macrolide antibiotics^29 30^ or, conversely, can decrease the use of antibiotics (when a viral infection is diagnosed and/or no bacterial infection is identified).^31^

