The treatable trait success story of chronic asthma certainly makes a case for the reappraisal of our approach to acute asthma.^6 7 43^ Is it time for precision medicine to attack the problem of asthma attacks? A worthwhile question, considering that corticosteroid toxicities appear after the lifetime equivalent of only four bursts (≥1000 mg cumulative dose) of prednisone—that is, four severe asthma attacks^44^—and the increasing levels of resistance to antibiotics observed, mainly due to inadequate prescriptions.^7 29^ Biomarker-guided management could avoid harm to individual patients and society stemming from the inappropriate use of OCs and/or antibiotics due to overuse or without proper consideration of their potential risks and side effects.^44 45^ Simply stated, corticosteroid and antibiotic stewardship can and should be assisted by acute POC testing.

Based on previous knowledge from chronic stable asthma and reports that asthma attacks are heterogeneous events, we hypothesise that treatment responses to OCs in acute asthma vary according to the underlying inflammatory phenotype. Specifically, we speculate that events identified by raised BEC and/or FeNO benefit most from OCs and that events presenting with low type 2 biomarkers have a lesser objective clinical and biological anti-inflammatory response but perhaps higher rates of airway infection or dysfunction. If this proves to be the case, we will be in a solid position to move forward with a randomised clinical trial comparing biomarker-directed OC use with the current ‘one-size-fits-all’ approach. An important secondary hypothesis of our study is that POC inflammatory and microbiological assessments in acute asthma are possible, acceptable and reliable. The ramifications of such findings would be to plan a clinical trial assessing biomarker-guided asthma attack management in primary care.

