### Study visits

Visit 1 will be on day 0 of the asthma attack, with oral prednisone issued by the community pharmacy (40 mg×7 days) (figure 1). Concomitant antibiotic use will only be considered for patients with ≥1 of the following criteria: CRP >20 mg/L, procalcitonin >0.25 µg/L (when available), or positive sputum culture and/or multiplex POC test for a significant bacterial pathogen. Healthy controls will attend only visit 1. Multimodal assessments performed at study visits lasting ~2 hours are detailed in table 1. In visit 1, these comprise:

Medical history and examination, including vital signs, inhaler technique and adherence check (using prescription refills of community pharmacy), five-item Asthma Control Questionnaire (ACQ-5),^46 47^ dyspnoea rated on the modified Medical Research Council Scale,^48^ Visual Analogue Scale for respiratory symptoms, Pittsburgh Vocal Cord Dysfunction Index,^49^ Nijmegen Questionnaire,^50^ Hospital Anxiety and Depression Scale,^51^ chest X-ray.FeNO measurement (NIOX VERO, Circassia) and pre/post-bronchodilator oscillometry (Tremoflo C-100, Thorasys Thoracic Medical Systems) and spirometry plus peak expiratory flow.Peripheral blood tests (complete blood count with differential, serum CRP, total and specific serum IgE, biobank), POC-BEC (Sight OLO, Sight Diagnostics), urine sample (creatinine, biobank), nasosorption with nasal epithelial lining fluid (NELF), nasal swab for the ultrarapid ID NOW (Abbott Industries) SARS-CoV-2 molecular test, nasopharyngeal swab for rapid multiplex PCR using the BIOFIRE Respiratory 2.1 (RP2.1) Panel (bioMérieux). If no spontaneous sputum is available, following negative COVID-19 testing and post-bronchodilator FEV_1_ > 60% predicted value or >1.5 L, induced sputum collection with hypersaline nebulisation would then be performed, as done in a previous asthma attack study.^37^

**Table 1 T1:** Study visit overview

Visit	Screening	0	1–6	7	97
Location	Telephone	Clinic	Home	Clinic	Virtual±telephone
Consent	Given	Signature			
Inclusion/exclusion criteria overview	x	x			
SARS-CoV-2 test (ID NOW)		x		x	
Medical history		x		x	x
Physical examination by doctor		x			
Inhaler technique check		x			
Adherence check (call to community pharmacy)		x			
Check if patient picked up prednisone tablets			x		
Review of test results by doctor				x	±
Questionnaires					
Medical Research Council dyspnoea scale		x		x	
Asthma Control Questionnaire (5 items)		x	x	x	x

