### Statistical analyses

Descriptive statistics will be presented for the complete sample and separated by groups (ie, frequencies and percentages for categorical, mean, and SD or median and IQR based on the distribution). The normality of variables will be assessed visually using Q–Q plots and histograms. Demographics will be compared between asthmatics and healthy controls using unpaired Student’s t-tests (Mann-Whitney) for continuous variables and Χ^2^ (Fisher’s exact test) for categorical variables. Due to the small sample size, no imputation methods are planned a priori for missing data. Frequencies and percentages of missing will be presented, and listwise deletion will be used for concerned analyses.

We will employ an unpaired two-sample t-test (Mann-Whitney U test if non-parametric) to assess the change in FEV_1_ (primary outcome) and ACQ-5 (key secondary outcome) between visits 1 and 2 according to type 2 inflammatory status. Additionally, to assess whether the observed change in FEV_1_ within subgroups defined by type 2 high events is clinically meaningful, we will employ a Χ^2^ test to compare the proportion of patients achieving the MCID between the two groups, using an MCID of 10% relative change in FEV_1_ and 0.5 points in ACQ-5. Finally, the above results will allow for a power calculation to plan a randomised controlled trial on key outcomes.

Exploratory analyses will include an association of the outcome measures with type 2 inflammatory mediators at visit 1 using further multivariable models. To consider the influence of potentially confounding variables, simple and multiple linear regression models will be performed for both independent variables (BEC and FeNO). Covariates considered are age, sex at birth, body mass index, atopic status, serum IgE, Asian race, nasal polyposis,^21^ smoking history, Charlson index, treatment intensity at baseline, exacerbation history in the past 12 months and ACQ-5. Only confounders associated (p<0.1) with FEV_1_ will be included in the final multivariable model. A linear mixed-effects analysis of the longitudinal improvements in parameters measured at home (FeNO, peak expiratory flows and symptom scores) according to baseline FeNO and BEC.

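### The covariate list for the BEC and FeNO regressions omits airway infection, which the Introduction itself raises as a confounder and visit 1 already measures

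*Protocol article*

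**What the plan says.** In the protocol article, Statistical analyses, the changes in FEV1 and ACQ-5 are compared by type 2 status with an unpaired t-test or Mann-Whitney test, without covariates. Confounding is left to simple and multiple linear regressions with BEC and FeNO as independent variables. The candidates are itemised: "Covariates considered are age, sex at birth, body mass index, atopic status, serum IgE, Asian race, nasal polyposis", then smoking history, then "Charlson index, treatment intensity at baseline, exacerbation history in the past 12 months and ACQ-5". Only those associated with FEV1 at p<0.1 "will be included in the final multivariable model".

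On infection, the Introduction asks how the type 2 phenotype affects the response to acute corticosteroids and goes straight on to say "An often-cited confounder is airway infection". It later supposes that type 2-low events have a smaller response but "perhaps higher rates of airway infection or dysfunction". The Abstract speculates that clinical and biological "response to those treatments varies according to inflammometry and microbiological test results". Under Study visits, "Concomitant antibiotic use will only be considered for patients with ≥1 of the following criteria"; these are raised CRP, raised procalcitonin, or a bacterial finding on culture or multiplex test.

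Infection is measured at visit 1. A multiplex PCR on a nasopharyngeal swab and CRP are scheduled for day 0, and culture is done when there is enough sputum (Table 1; Specimen processing and analysis).

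**The concern.** The list is explicit and comes with a retention rule, so this is a choice the article makes and not a detail left to a fuller document. The one factor that the Introduction calls a confounder is not on it.

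If infection is more frequent in one type 2 group, and infected events recover differently by day 7, part of that difference will appear as a type 2 difference. Antibiotic use may also differ between the groups, because it is tied to infection and inflammation markers. The Introduction intends to read the contrast as a difference in response to corticosteroids and to build a randomised trial on it. Readers would then want to see how much of the contrast goes with infection, and no listed analysis shows them.

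**Working it through.** **1. Search for an infection term.** The list has 7 items in its first part, then smoking history, then 4 more: 7 + 1 + 4 = 12. None is an infection result, CRP or antibiotic use. The other analyses do not fill the gap:
- The t-tests are unadjusted.
- The mixed model for home data is by baseline FeNO and BEC only.
- The sensitivity analyses concern sex, gender and diversity.
- Microbiome diversity is an exploratory parameter to be related to BEC and FeNO, not an adjuster.
- The key-message box promises to explore "microbiological parameters and treatment response", but that does not adjust the type 2 comparison.

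**2. Scale of the planned effect.** The Sample size section assumes a difference of 10 points, SD 10, 1:1 groups, two-sided α 0.05 and 90% power. The noncentral t calculation gives 22.02 per group, rounded up to 23, so n=46 with power 91.2%. The stated figure reproduces and is not in dispute.

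**3. Possible shift (all infection inputs assumed).** The documents give no infection rates or effects. Shift = prevalence gap between type 2 groups × effect of infection on FEV1 change.

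| Gap | Effect (points) | Shift (points) |
|---|---|---|
| 0.1 | 5 | 0.5 |
| 0.3 | 5 | 1.5 |
| 0.3 | 10 | 3.0 |
| 0.4 | 10 | 4.0 |

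The low end is negligible. The high end needs an infection effect as large as the whole planned type 2 effect.

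**4. Precision cost of one infection covariate.** With equal groups and mean prevalence m, the correlation of infection with type 2 status is r = 0.5 × gap / √(m(1−m)). Variance inflation is 1/(1−r²), and the standard error grows by its square root.
- 40% v 30%: inflation 1.01, standard error up 0.6%.
- 50% v 20%: r = 0.15/√(0.35 × 0.65) = 0.314, inflation 1.11, standard error up 5.3%.
- 60% v 20%: inflation 1.20, standard error up 9.5%.

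This ignores any gain from explaining outcome variance.

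**5. The p<0.1 screen.** Suppose 16 of 46 patients are infected, SD is 10, and the screen is applied to FEV1 change (the text says only FEV1). Infection would be kept in 48% of studies if its effect were 5 points and in 94% if it were 10. Adding it to the list without exempting it from the screen would therefore be unreliable for moderate effects.

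**6. Imperfect measurement.** One simulated scenario had 23 per group, infection in 50% of type 2-low and 20% of type 2-high events, an effect of −10 points, and no type 2 difference net of infection. The unadjusted contrast averaged 3.0 points. Adjustment brought it to 0.0 with perfect infection status, and to 1.6 with a test of 80% sensitivity and 90% specificity.

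**The case against.** The strongest reply is that the documents never say infection alters FEV1 recovery on prednisone. After naming infection as a confounder, the Introduction discusses only antibiotics. It then pairs corticosteroid response with type 2 phenotype, and antibiotic response with infection. The Abstract sentence can be read the same way, and the link to type 2-low events is hedged. This stands. A reader might infer that the protocol itself establishes both conditions for confounding, but it only raises the possibility.

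Second, infection may be part of what makes an event type 2-low, so adjustment could remove some of the contrast of interest. For biomarker-directed prescribing the unadjusted difference is the relevant one. This also stands, and it is why both estimates should be shown and neither should replace the other. Nor can adjustment separate corticosteroid response from natural recovery, since prednisone is planned for every patient.

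Third, the list serves exploratory regressions in a pilot whose Sample size section already calls such analyses likely underpowered and in need of confirmation. That limits the weight of the point. It does not explain why a factor named as a confounder and already measured should be left out.

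Fourth, SARS-CoV-2-positive events are excluded. That removes one infection; other viruses and bacteria remain.

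**Conclusion.** The omission is real and worth correcting as a cheap improvement. The explicit list of 12 leaves out a factor that the Introduction names as a confounder and visit 1 measures, and no other listed analysis adjusts the type 2 contrast for it.

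Whether infection confounds the contrast, by how much and in which direction, cannot be learned from the documents. The shift of 0.5 to 4 points against a planned 10 is an illustration resting wholly on assumed prevalence gaps and effects; it could exaggerate or mask a difference.

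A reader might also infer that the primary test has a faulty error rate or power that this change would repair. The documents do not support that: they contain no infection figures, and the change leaves the t-test as it is. What is gained is interpretation, namely how far the type 2 difference goes with infection.

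**What to change.** In Statistical analyses:

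- Add visit 1 airway infection status to the covariates and keep it in the model regardless of the p<0.1 screen.
- Define it mainly from the day 0 multiplex PCR (any virus or bacterium detected), plus a positive sputum culture where one was obtained. A missing culture should not make the variable missing, because listwise deletion applies. The antibiotic criteria should not serve as the definition: they would code a patient with only a virus detected as uninfected.
- As a supportive analysis, report the type 2 difference in FEV1 change and in ACQ-5 change with and without infection status.
- Tabulate antibiotic use by type 2 group, descriptively, since it follows visit 1 results.
- Leave the primary t-test unchanged.

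The cost is two or three sentences and no new test. The models lose one or two degrees of freedom, and the standard error of the type 2 difference rises by about 1% to 10% under the assumed gaps. Misclassified infection status would leave part of any confounding in place, and the report should say so.

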Visual Analogue Scale of asthma symptoms (6 items)		x		x	
Pittsburgh Vocal Cord Dysfunction Index		x		x	
Nijmegen Questionnaire		x		x	
Hospital Anxiety and Depression Scale		x		x	
Survey of % of home tests monitored				x	
Satisfaction questionnaire about point-of-care biomarker measurements: participant				x	
Satisfaction questionnaire about point-of-care biomarker measurements: letter and email sent to treating doctor				x	
Respiratory physiology					
FeNO measurement (NIOX)		x		X	
Teaching of FeNO measurement		x			
FeNO measurement		x	x	x	
Teaching of peak expiratory flow measurement		x			
DEP measurement		x	x	x	
Capillary blood eosinophils: sight OLO measurement		x		x	
Force spirometry—pre-bronchodilator		x		x	
Forced oscillation—pre-bronchodilator					
Salbutamol 400 µg		x		x	
Force spirometry—post-bronchodilator		x		x	
Forced oscillation—post-bronchodilator					
Inflammometry					
Hospital viral multiplex PCR (BIOFIRE on nasopharyngeal swab)		x		x	
Nasosorption		x		x	
Nasal cytology brushes		x		x	
Induced or spontaneous sputum collection for differential cell count+supernatant, plugs and cell pellet for biobank		x		x	
Induced or spontaneous sputum collection for hospital microbiology analysis		x		x	
Hospital blood tests (1 EDTA tube, 1 heparin tube): complete blood count with differential, C reactive protein		x		x	
Allergy testing (hospital blood tests; 1 tube) for total serum IgE, specific serum IgE: grass mix, weed mix, tree mix, mould mix, house dust mites *Dermatophagoides pteronyssinus* and *D. farinae*, *Aspergillus fumigatus*		x			
Research laboratory blood tests: 1 EDTA, 4 heparin, 2 serum, 1 whole blood for research laboratory (biobank)		x		x	
Chest X-ray		x			
Urine sample; urine creatinine for hospital; sample frozen for research laboratory (biobank)		x		x	

FeNO, fractional exhaled nitric oxide.

Visit 2 will additionally include a survey of adverse events relating to corticosteroids, patient satisfaction questionnaires and permission to contact the patient’s primary care provider for a physician survey about POC testing.

Visit 3 is a web-based survey reviewing the number of subsequent exacerbations, medication changes and ACQ-5 score and allowing the patient to prompt a call from the study team (or vice-versa if the study team has a test to follow up on).

All study visits will occur in the morning to avoid the confounding effect of circadian variation of type 2 inflammatory biomarkers.^51–53^

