### Home monitoring

Between visits 1 and 2, patients will be invited to complete daily symptom scores, FeNO and peak expiratory flow measurements via a paper diary card.

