#### Exploratory outcomes

The continuous association between baseline biomarkers (BEC and FeNO) and changes in symptom scores, sputum inflammometry, additional lung physiology parameters (impulse oscillometry), inflammatory mediators (type 2 cytokines, chemokines, alarmins, eosinophils) and microbiome diversity across different immune compartments (nasal epithelium, induced sputum, serum, urine).Comparative agreement and reliability of gold-standard BEC (hospital laboratory) versus POC test (Sight OLO).An appraisal of POC biomarkers using patient satisfaction scores and primary care physician surveys.A sensitivity analysis on all of the above assessing how sex at birth, gender (self-identified: female, male, other specify) and race (self-identified)^59^ influence treatment responses.

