### Sample size

For our primary analysis, assuming a two-sided α error of 0.05, a T2:non-T2 event ratio of 1:1 and a mean±SD population difference in δ FEV_1_ of 10±10%, n=46 will provide 90% of power to detect the difference in our primary outcome on an unpaired two-sample t-test. According to a recent Canadian study that assessed the proportion of randomly selected adults with physician-diagnosed asthma who fulfil objective criteria to confirm the diagnosis of asthma, 18.3% of participants reporting a severe asthma attack in the past year (11 of 60) did not have asthma confirmed.^61^ We thus conservatively estimate that 20% of patients recruited will not count towards the n=50 needed for the primary analysis.

Including a cohort of 12 healthy control participants, each assessed during a single visit, is intended to enhance our ability to relativise demographics, lung function and inflammatory measurements observed in the study. Recruitment will continue until the target number of confirmed asthmatics and healthy controls has completed the study.

We acknowledge that the secondary and exploratory analyses will likely be underpowered and view these as exploratory but feasible within the proposed timeline of a pilot study serving to plan further clinical trials. Any significant finding for secondary and exploratory outcomes will require further confirmatory studies to support them.^62^

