## Discussion

The proposed observational and translational before/after pilot study of asthma attacks across the range of asthma severities will be the first to focus on the role of BEC and FeNO and explore the clinical and biological factors affecting OC treatment response in acute asthma. We view our pilot study of POC measurements for assessing type 2 inflammation and airway infection as a stepping stone to plan a clinical trial allowing for biomarker implementation in the primary care setting. Biomarker-guided management could avoid harm to individual patients and society stemming from inappropriate use of OCs and/or antibiotics.

We expect events identified by raised BEC and/or FeNO to benefit most from corticosteroids, and POC tests to be useful theragnostic and mechanistic tools. Specifically, we expect increased BEC and FeNO to predict greater improvements in (a) FEV_1_ (primary outcome), (b) ACQ-5 scores (key secondary outcome), and (c) inflammatory mediators, symptoms, and other physiological aspects (exploratory outcomes). If the study hypothesis is confirmed—a phenotypical variability in treatment responses associated with type 2 airway inflammation—then the utility of BEC and FeNO could be studied to manage asthma attacks in a randomised controlled trial.

Three distinct studies in asthma attacks are underway, each with its unique objectives. ExCluSie-F (Phenotyping and Classifying Asthma Exacerbations; NCT05304039) is a prospective cohort that will explore the association between phenotypical characteristics and a composite outcome of treatment effectiveness. On the other hand, ‘APEX’ (Asthma: Phenotyping Exacerbations; NCT04293588) is a longitudinal cohort with participants who have experienced at least one asthma exacerbation in the previous year that aims to assess the proportion of patients displaying eosinophilic and non-eosinophilic phenotypes. Lastly, ‘BOOST’ (Recovery of Breakthrough Asthma Attacks Treated with Oral Steroids While on Monoclonal Antibody Therapy) is a prospective observational study involving adults on long-term biological treatment for asthma that will compare clinical recovery between individuals with high FeNO levels during their asthma attacks and those with low FeNO.^63^

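### The home-monitoring model relates baseline FeNO to improvement in FeNO itself, so regression to the mean can pass for a biomarker-predicted response

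*Protocol article*

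**What the plan says.** The Statistical analyses section of the protocol article plans a linear mixed-effects analysis of "longitudinal improvements in parameters measured at home (FeNO, peak expiratory flows and symptom scores) according to baseline FeNO and BEC". Under Home monitoring, "patients will be invited to complete daily symptom scores, FeNO and peak expiratory flow measurements via a paper diary card", so FeNO is measured at home and the blood eosinophil count (BEC) is not.

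Table 1 (Study visits) has a row "FeNO measurement (NIOX") for days 0 and 7, and a second FeNO row for days 0, 1-6 and 7. The article does not say which of the two day-0 readings is the baseline in the model, or whether day 0 is also the first point of the outcome series.

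The first exploratory outcome is "The continuous association between baseline biomarkers (BEC and FeNO) and changes in symptom scores, sputum inflammometry" and further measures, among them "inflammatory mediators (type 2 cytokines, chemokines, alarmins, eosinophils"), across nasal, sputum, serum and urine compartments. In the Discussion, "we expect increased BEC and FeNO to predict greater improvements in" FEV1, ACQ-5 and "(c) inflammatory mediators, symptoms, and other physiological aspects (exploratory outcomes)".

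**The concern.** A person whose day-0 FeNO happens to be high, through reading error or a passing rise, will on average read lower later. Someone who happens to be low will read higher. When change is related to the same starting value, this alone links a higher baseline to a larger fall. No difference in steroid responsiveness is needed.

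The direction matters. The artefact points the same way as the hypothesis that raised type 2 markers go with a greater biological response. A significant coefficient for baseline FeNO on FeNO improvement could therefore be cited in support of that hypothesis and carried into the planning of the randomised trial. The false discovery rate control planned for inflammatory mediators would not protect against this. It assumes that each p-value is valid when there is no differential effect, and here it would not be.

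**Working it through.** **The plan's own figure.** The article gives no figure for this model. The only sample-size figure is for the primary FEV1 comparison. With a difference of 10, SD 10, two-sided 0.05 and 90% power, the t-test needs 22.02 per group, hence 23 per group and 46 in total, as stated (power 91.2%). It is not in dispute.

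**Inputs.** n=50 is the target in the Sample size section, and alpha is 0.05 two-sided. The between-visit correlation, the SD ratio and the share of day-to-day variation are not in the article, so they are assumed and shown as ranges.

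**Step 1: two time points.** Let X be baseline, Y follow-up, rho their correlation and k the SD ratio (follow-up to baseline). Then

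corr(X, Y-X) = (rho·k - 1) / sqrt(1 + k² - 2·rho·k).

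For k=1 this is -sqrt((1-rho)/2). By Fisher's z, the chance of p<0.05 is about Φ(|atanh r|·sqrt(47) - 1.96), plus a negligible opposite tail.

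| rho (assumed) | r | \|atanh r\|·sqrt(47) | chance of p<0.05 |
|---|---|---|---|
| 0.5 | -0.50 | 3.77 | 96% |
| 0.7 | -0.39 | 2.80 | 80% |
| 0.9 | -0.22 | 1.56 | 34% |

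The SD ratio matters too. For rho from 0 to 0.9, k=0.7 gives r between -0.71 and -0.82, part of which is a real narrowing of spread. With k=1.3, r runs from -0.61 to +0.29.

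**Step 2: a daily series, closer to the planned model.** Take one reading a day on days 0-7, the same fall in everyone, total variance 1 on each day, and a share ICC of that variance lying between persons. The least-squares slope gives day 0 a weight of -3.5/42. If day 0 is also the predictor and daily errors are independent,

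corr(baseline, slope) = -(3.5/sqrt(42))·sqrt(1-ICC) = -0.540·sqrt(1-ICC).

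That is -0.45 at ICC 0.3 and -0.17 at ICC 0.9. Simulation at n=50 (1,000 runs each) gave the same values, with false-positive rates of 93% and 21%. With day-to-day autocorrelation of 0.5 the range was -0.50 to -0.19, with rates of 96% to 25%. Per-person slopes stand in here for the baseline-by-time term of the mixed model.

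**Step 3: variants that avoid the shared reading.**
- Separate baseline reading with independent error: r about 0, false-positive rate 5-6%.
- Day 0 used as predictor only, no autocorrelation: r about 0, rate 4-7%.
- Day 0 used as predictor only, autocorrelation 0.5: r from -0.25 to -0.09, rate 46% to 9%.
- Separate same-day reading that shares a fraction f of the within-person variance as true day-0 fluctuation: r = -0.540·f·sqrt(1-ICC). For ICC 0.5, 0.7 and 0.9, f=0.5 gives r of -0.19, -0.15 and -0.09, and rates by the Step 1 formula of about 26%, 18% and 9%. With f=0.75 the rates are about 52%, 34% and 14%.

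A second device therefore removes the artefact only to the extent that within-person variation is device error. Dropping day 0 from the outcome series removes it only if readings on neighbouring days are not correlated beyond the stable person effect.

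**The case against.** The strongest reply is that the baseline may not be part of the outcome at all. Table 1 lists the NIOX reading apart from the home-series reading, and the model concerns home measurements. On that reading, with independent errors, the false-positive rate is nominal. How a mixed model is set up is also commonly left to a statistical analysis plan.

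Part of this stands: the article does not fix the worst case. But Table 1 also marks the home-series row at day 0, and nothing says which reading is baseline. Patients are enrolled during an attack, so two readings at the same visit may well share a transient rise. The pairing of FeNO with its own baseline is stated in the article, not merely left open.

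The limited weight of the analysis is also a fair point. It is exploratory, and "Any significant finding for secondary and exploratory outcomes will require further confirmatory studies to support them". FeNO is not named among the outcomes expected to improve in the Discussion; it would enter only under the general terms there. Confirmation does not cure this fault, however, because a second study using the same model would reproduce the artefact. Patients may also decline the diary and still take part, so n may be below 50. That lowers the false-positive rate but leaves r unchanged.

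Three stronger readings are tempting and are not supported.
- A reader might infer that BEC has the same fault. The home model has no BEC outcome, and the word eosinophils in the exploratory list is not tied to venous blood.
- A reader might infer that a significant result is near certain, or that r approaches -1 if treatment brings everyone to a uniformly low level. The first fails over much of the range above. The second describes a real shrinkage of spread, and for a marker whose own-baseline analysis is not shown to be planned.
- A reader might extend the point to peak flow and symptom scores. These are not arithmetically coupled to baseline FeNO or BEC.

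**Conclusion.** The concern holds for FeNO only. As worded, the plan relates baseline FeNO to improvement in FeNO and so can produce a significant negative association with no differential steroid effect. With day 0 on both sides of a slope model, the false-positive rate is about 21% to 93% for ICC between 0.9 and 0.3. It is about 5% when the baseline is a separate reading with independent error, and intermediate when same-day fluctuation is shared. These figures rest on n=50, equal SDs and assumed correlations; the article supplies none of the last two. The consequence is a possible misreading of one exploratory result. The primary FEV1 comparison and its sample size are untouched, so this is a minor point, though cheap to put right.

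**What to change.** - Do not use baseline FeNO as a predictor of change in FeNO as evidence of differential response. Report FeNO over time descriptively, as levels and geometric mean ratios.
- If the question is to be kept, name a method that allows for coupling and regression to the mean, state which day-0 reading is the baseline, and keep day 0 out of the outcome series. Keeping it out is not sufficient by itself, as the autocorrelated case in the working shows.
- Keep baseline BEC as a predictor of home FeNO, adjusted for the day-0 FeNO value. Keep baseline FeNO and BEC as predictors of peak flow and symptom scores.
- Say whether eosinophils in the first exploratory outcome includes venous blood eosinophils. If it does, apply the same rule to baseline BEC.

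The cost is a change of analysis wording and one fewer exploratory test. No data collection changes.
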